#### Questionnaires

The following cross-sectional questionnaire data will be collected during the military call-ups: 1) health survey consisting of questions related to health behaviour, diet, sleep, psychosocial and socioeconomic factors, quality of life, depressive symptoms (Raitasalo’s modification of the short form of the Beck Depression Inventory [51,52], and substance abuse; 2) amount of physical activity [47] and sitting time, self-rated physical fitness, 3) relationship to physical activity: a questionnaire focusing on physical activity or lack thereof, and the underlying motives, 4) information behaviour and practices in relation to the stages of change of the transtheoretical model [38,39], the use of media, games and technology.

#### Ethnographic and interview data

Participant observation and subject interviews are conducted in several phases. Firstly, the objective is to understand specific values, motivations and cultural meanings in general in youth culture which affect adolescent’s health behaviour [53]. Secondly, an in-depth description is constructed based on their experiences and opinions of the intervention in order to improve the methods further [54,55]. In this way the ethnographic work also provides feedback between the target group and service developers.

#### Measurements

Height will be measured with a ruler. Waist circumference will be measured midway between the lowest rib and the iliac crest. Body composition (fat mass, fat free mass, percentage body fat), BMI and weight will be assessed by bioelectrical impedance assessments (DSM-BIA; direct segmental multi-frequency bioelectrical impedance analysis). For this purpose InBody 720 Body composition analysis (Biospace Co., Ltd., Seoul, Korea) will be used. The accuracy of measurement is high in comparison to e.g. the dual-energy x-ray absorptiometry (DXA) method [56] and practical in large epidemiological studies with limited time for examining each subject [11]. Bilateral grip strength of both hands will be measured using a dynamometer (Saehan, SAEHAN Corporation, Korea). During the examination, the subjects stand with their legs apart and elbow at 90° angle, and grip the instrument with maximum strength.

Aerobic fitness will be evaluated using a fitness test (Polar Fitness Test™, Polar Electro, Finland) conducted while resting comfortably during ca. 5 minutes. The Polar Fitness Test™ predicts maximal oxygen uptake (ml/min/kg) from the resting heart rate, heart rate variability, gender, age, height, body weight and self-assessed physical activity [57]. Heart rate variability (R-R intervals) will be measured from 255 heart beats (3–5 min) with a sampling frequency of 1000 Hz [58]. During the military service, all conscripts undergo muscle fitness tests [12] performed twice by the FDF. Aerobic fitness with Cooper’s 12-minute running test [40] will be performed at the beginning and end of the military service.

### Statistical analysis

Descriptive analyses will be performed utilising the results of the questionnaires and measurements. Absolute and percentage changes from baseline will be calculated for continuous variables. The paired samples t test will be used to compare means of the within group change from baseline, and the t test for independent samples will be used to compare means between the treatment and the control group. The analysis of variance for repeated measures will be used to analyse the intra-group-by-time-effect and the group-by-time interaction and to adjust for possible confounding factors over the study period. The changes in activity and weight during the trial and follow-up will also be examined by multiple linear regression analyses with generalized estimation equations (GEE) to account for correlations between repeated measurements. Association between the response and explanatory factors in the aggregated data will first be analysed using cross tabulation and the Pearson product–moment correlations. Multiple linear and logistic regression analysis using all variables associated with activity level and weight in univariate analyses will be performed to evaluate the determinants of change within the exercise group and the pooled groups. Data will be analysed using both intention to treat and per protocol basis.

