### Setting and randomization

The recruitment is performed at the call-ups for military service in Oulu arranged by the Finnish Defence Forces and City of Oulu every September. Oulu (65°N 25°E) is a growing university town in the northern Finland of approximately 190 000 inhabitants, of which a substantially high proportion are children and adolescents. The unemployment rate of the young people (<25 years) is relatively high in Oulu (19%) compared to other areas in Finland (14%) [36]. Conscription-aged men provide a large, population-based representative sample of young men. All those determined fit for service, who are granted postponement or are exempted from service (n = 1500) will be included in the intervention study. Annually approximately 35% of the conscription aged men in Oulu area are exempted from service, which is the highest proportion in Finland. Adolescents and young men exempted from compulsory military or civil service comprise of a group with a wide range of psychosocial problems and are a target population for supportive interventions [37]. Based on experience for pilot study conducted in 2011, it is estimated that approximately 15% of the men refuse to participate. Thus, approximately 1280 men are expected to participate. These will be randomly allocated into an intervention (n = 640) and control group (n = 640) using computer-generated random numbers. With an estimated 30% dropout rate there will be 447 boys in each group at the end of the intervention.

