### Intervention

The 6-month intervention will commence at the call-ups (Figure 1). The activation group utilises the abovementioned online gamified activation platform service, whereas the subjects in the control group will continue their normal lives. All subjects will carry a physical activity monitor and the activity data are saved in a database. The control subjects will use blinded monitors which will not provide any feedback for the participants. The questionnaires and measurements will be repeated at the end of the intervention (6 months). The trial protocol and gamified activation service will be pilot tested in 2012 with a smaller sample.

After the intervention the subjects’ entry into military service will be followed up for a period from 18 to 30 months depending on the initiation and length (6–12 months) of service. The course of the service period will be monitored by the Finnish Defence Forces (FDF) which routinely collects data on health and performance of all conscripts attending service. The group assignment will be blinded to the FDF until the end of military service. Examinations measuring aerobic (Cooper - 12 minute running test) [40] and muscle fitness tests [12] are performed when entering service and repeated after its completion. These data will be collected from approximately 70% of the men due to the estimated exemption. This will provide additional information about the impact of the intervention and show the long-term effectiveness of the method aimed at promoting physical activity. It also demonstrates how the activation intervention affects the onset and completion of military service.

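### Baseline is nowhere stated as a covariate in the between-arm analyses, which costs precision, and the autumn-to-spring within-arm tests cannot separate the intervention from season

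*Protocol article*

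**What the plan says.** The Statistical analysis section of the protocol article sets out the following, in this order, and does not say which analysis is primary.

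- Change measures: "Absolute and percentage changes from baseline will be calculated for continuous variables".
- Within each arm: "The paired samples t test will be used to compare means of the within group change from baseline".
- Between arms: the "t test for independent samples will be used to compare means between the treatment and the control group". No covariate is attached to this test, and the response (change or six-month value) is not named.
- A repeated-measures ANOVA is to analyse the effect of time within groups "and the group-by-time interaction and to adjust for possible confounding factors over the study period".
- Changes in activity and weight are also to be examined by "multiple linear regression analyses with generalized estimation equations (GEE) to account for correlations between repeated measurements".

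No section names the baseline value of an outcome as a covariate in any of these models.

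On timing, the Setting and randomization section places recruitment at call-ups "arranged by the Finnish Defence Forces and City of Oulu every September", in a city at 65°N. The Intervention section starts the intervention at the call-ups and repeats the questionnaires and measurements six months later, which is about March. Both arms are measured at both times and both carry a monitor; the control monitors give no feedback.

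**The concern.** Two separate matters arise from the tests as stated.

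The first is efficiency. The trial collects questionnaire and physical measurements at the call-ups. A two-sample t test that ignores them, or that only subtracts them, uses the baseline less well than a regression of the six-month value on arm and baseline. The group-by-time term does not change this for outcomes measured twice, because without covariates it is the same test as the t test on change. What is at stake is precision that would cost nothing to gain.

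The second is interpretation. Daily physical activity may well differ between September and March at that latitude. A paired test within one arm picks up any such shift together with any intervention effect. These tests come first among the inferential methods and are not labelled descriptive, so a significant change in one arm and not in the other could be taken as evidence of an effect.

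**Working it through.** **Inputs.** From the article: 335 per group required, with 80% power and 5% significance (Sample size); 447 per group expected at the end (Setting and randomization). Not in the article, so assumed: the correlation r between baseline and six-month values (0.3 to 0.9), equal SDs at the two times, and the size of any seasonal shift.

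**1. The plan's own figure.** [27.6 × 72.4 + 18.5 × 81.5] / 9.1² × 7.9 = 3505.99 / 82.81 × 7.9 = 334.5, rounded up to 335. It reproduces. It is a calculation for two proportions, so nothing below alters it.

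**2. Equivalence.** With two time points and no covariates, the group-by-time F statistic equals the square of the t statistic for the between-arm difference in change. The ANOVA therefore gains precision over the change-score test only if a useful covariate, such as baseline, is added.

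**3. Relative variance.** In units of the outcome variance, the per-arm variance is 2(1 − r) for a change score, 1 for the six-month value and 1 − r² for ANCOVA. The ratios are (1 − r²) / [2(1 − r)] = (1 + r)/2 against change scores, and 1 − r² against six-month values. Both are shown because the article does not say which response the t test uses.

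| r (assumed) | ANCOVA / change score | ANCOVA / six-month value | ANCOVA power where the change-score test has 80% |
|---|---|---|---|
| 0.3 | 0.65 | 0.91 | 93.5% |
| 0.5 | 0.75 | 0.75 | 89.9% |
| 0.7 | 0.85 | 0.51 | 86.0% |
| 0.9 | 0.95 | 0.19 | 82.0% |

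The detectable difference at 80% power with 447 per arm is (1.96 + 0.84) × √(2v/447) SD, where v is the variance above. At r = 0.5 it is 0.187 SD for change scores and 0.162 SD for ANCOVA; at r = 0.7 it is 0.145 and 0.134 SD.

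**4. Season and the within-arm tests.** Suppose there is no intervention effect and both arms shift by s SD. The standard error of mean change in one arm is √[2(1 − r)/447]. At r = 0.5 this is 0.0473. A shift of 0.1 SD then gives an expected z of 2.11 and a significant paired test 56% of the time; 0.2 SD gives 99%. At r = 0.7 the figures are 78% and over 99%. At r = 0.5 and s = 0.1, exactly one of the two independent arms is significant with probability 2 × 0.56 × 0.44 = 0.49, although nothing differs between them.

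**5. Season and the between-arm test.** In 2,000 simulated trials with 447 per arm, a common shift of 0.2 SD and no effect, the t test on change rejected 5.05% of the time at r = 0.5 and 4.7% at r = 0.7. The shift cancels. The simulated ANCOVA to change-score variance ratios were 0.76 and 0.84, against 0.75 and 0.85 from the formula.

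**6. Monitor outcomes.** The intervention and the monitoring both begin at the call-ups, and the article describes no monitor recording before the service starts. If questionnaire activity has to serve as the covariate, (1 + r)/2 no longer applies. The variance relative to an unadjusted six-month comparison is 1 − q², where q is the correlation of the questionnaire with the monitor outcome. The article gives no q; at q = 0.3 the ratio would be 0.91.

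**The case against.** The strongest reply is that the section does not stop at t tests. It plans confounder adjustment within the ANOVA and a GEE regression, and an article may leave the covariate list to a fuller document. That stands in part: the missing list is not itself a fault, and baseline could yet be among the covariates. But the adjustment clause is aimed at confounding over the study period, the GEE is described as handling within-person correlation, and no primary analysis is chosen. The one between-arm test specified without covariates remains on an equal footing with the rest.

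Several stronger readings are tempting and are not supported.

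- A reader might infer that the arms are tested on percentage change. The article says only that percentage changes are calculated, and assigns no test to them.
- A reader might infer that season biases the trial's result. Both arms share the season, the hypotheses compare the arms, and a group-by-time test is planned. The article nowhere says that efficacy will be read from the within-arm tests.
- A reader might expect many zero baselines for vigorous time, on the view that the trial enrols inactive men. It enrols call-up men generally, and no distribution of vigorous time is given.
- A reader might conclude that the trial could be 15% to 35% smaller. Those savings apply to r of 0.3 to 0.7 and a same-variable covariate. At r = 0.9 the saving against change scores is 5%, and the planned size rests on proportions.

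**Conclusion.** The point holds as an efficiency improvement and a matter of labelling. The stated between-arm tests are valid, and no bias in the randomised comparison is shown. Under equal SDs, ANCOVA on the same variable reduces the variance by 35% to 5% against change scores, and by 9% to 81% against six-month values, as r runs from 0.3 to 0.9. Every value of r here is an assumption. The gain for monitor outcomes without a pre-intervention recording cannot be sized from the article and is likely to be smaller. The within-arm paired tests cannot separate the intervention from season; how far that matters depends on a seasonal shift for which the article gives no figure. The sample size is unaffected.

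**What to change.** - Name one primary between-arm analysis for each continuous outcome: an ANCOVA, or an equivalent mixed model, of the six-month value on arm plus the baseline value of the same variable, where that value is collected before the service starts. This covers questionnaire activity, sitting time, weight and the other call-up measurements. Report the adjusted difference with its 95% confidence interval.
- For monitor outcomes with no pre-intervention recording, use baseline questionnaire activity as the covariate, and do not claim the same-variable gain for them.
- Label within-arm changes as descriptive, and draw conclusions about the intervention only from the between-arm comparison.
- State that percentage change is not used for between-arm inference. It is undefined at a zero baseline and unstable near zero.

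The cost is a few sentences in the protocol and the analysis plan. No new data, visits or participants are needed.

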### Sample size

The primary outcome variable is the change in the time spent in physical activity of different intensities (sedentary, light, moderate and vigorous). The aim is to lower the proportion of inactive men by one third in the intervention group with no change in the control group. At baseline, the estimated number of inactive men is 212 (27.6%, data from the 2009 call-ups). With study power of 80% and significance level of 5%, the calculated sample size is [(27.6 × (100–27.6) + 18.5 × (100–18.5)]/[(27.6-18.5)^2^] × 7.9 = 335 persons/group.

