## Discussion

The results of this study will provide evidence on the effectiveness of the online gamified activation service for increasing the activity and reducing inactivity in young men. This is the first study to combine a gamified service with objective continuous measurement of physical activity in daily life; i.e. also when the subject is not using the service. The study also provides novel information on the health status, physical fitness, motivational factors and profiles of physically active and inactive young men. This information can be utilized in future development of tailored gamified services. Promotion of physical activity at young age provides an early intervention for preventing any future adverse health effects. Hence, the produced physical activation method has broad public health significance.

The developed new model of gamification used for promoting physical activity will provide a new approach for reaching young people. Tailored health messages are delivered based on applying the transtheoretical model that is augmented with the concept of information behaviour to identify the participants’ stages of exercise behaviour change. This study will explore new possibilities to direct the health behaviour of young men without many times ineffective and provoking top-down coercive health instructing, which may have opposite effects that was intended among adolescents [59]. For finding new, affecting, and at same time entertaining and socially acceptable means for adolescents, their active participation to the development process is essential. The produced gamified platform may exert other positive social effects which may directly or indirectly improve health and wellbeing.

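### The determinants-of-change models select variables by univariate tests and then test them in the same men, so the p-values and intervals of the selected variables are not valid as they stand (secondary analysis, minor)

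*Protocol article*

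**What the plan says.** The protocol's Statistical analysis section sets out two steps. First: "Association between the response and explanatory factors in the aggregated data will first be analysed using cross tabulation and the Pearson product–moment correlations". Second: "Multiple linear and logistic regression analysis using all variables associated with activity level and weight in univariate analyses will be performed", and the purpose is "to evaluate the determinants of change within the exercise group and the pooled groups". The rule is therefore written down: association in a univariate analysis is the entry criterion, and everything that meets it enters.

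The two sentences do not name the same screening response. The second speaks of association with activity level and weight; the first speaks of association with the response, which for these models would be change.

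The candidate pool is wide. Under Questionnaires, one of four blocks alone is a "health survey consisting of questions related to health behaviour, diet, sleep, psychosocial and socioeconomic factors, quality of life" and more. Measurements adds body composition, waist, grip strength, heart rate variability and predicted oxygen uptake. The cut-off, the number of candidates and the binary outcome of the logistic model are not given.

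**The concern.** The men who decide which variables enter are also the men in whom those variables are tested. Second-step p-values and intervals treat the entered variables as if they had been chosen in advance. Variables that passed by chance carry that chance into the second step, and the coefficients of selected variables tend to be too large. A variable that matters only jointly with others can be lost at the first step.

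With these numbers the entry bar is low. At an assumed two-sided 5% cut-off, a correlation of 0.093 suffices in one group and 0.066 in both groups pooled. At stake is the credibility of the list of determinants that the trial would publish. The efficacy conclusion is not at stake.

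**Working it through.** **Inputs from the protocol.** Inactive at baseline 27.6%, target 18.5% in the intervention group, power 80%, significance level 5% (Sample size); 447 men per group after dropout, so 894 pooled (Setting and randomization).

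**The plan's own figure.** [27.6 × 72.4 + 18.5 × 81.5] / 9.1² × 7.9 = (1998.24 + 1507.75) / 82.81 × 7.9 = 334.5, hence 335 per group as stated. The protocol gives no figure for the determinants models.

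**Assumptions, because the protocol is silent.** Screening cut-off p < 0.05; 30, 60 or 100 candidates; correlation 0.1 between candidates; correlation 0.6 between baseline and month 6. For scale, the Questionnaires and Measurements sections name about 18 constructs and about 11 measurements, so about 29 before single items are counted.

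**Entry bar.** Critical r = t / √(n − 2 + t²). For n = 447: 1.965 / √(445 + 3.86) = 0.093, or 0.9% of variance. For n = 894: 1.963 / √(892 + 3.85) = 0.066, or 0.4%.

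**Error rate of a noise variable that has entered** (linear model for change, n = 447, no candidate a true determinant, nominal rate 5%):

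| Screen | Called a determinant, given entry |
|---|---|
| On level, baseline not in the model | about 12–14% |
| On level, baseline added to the model | 5–6% |
| On change | about 49–68% |

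Repeat runs differ by one or two percentage points, and n = 894 gives similar results.

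The first two rows differ for a simple reason. With equal variances, the correlation between change and baseline is (0.6 − 1) / √(2 − 2 × 0.6) = −0.4 / 0.894 = −0.45. A variable that happens to correlate with baseline level therefore also correlates with change until baseline is in the model.

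**Chance of at least one false determinant in a model:**

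| Candidates | 30 | 60 | 100 |
|---|---|---|---|
| Noise variables entering (level screen) | 1.5 | 3.0 | 4.9 |
| Screen on level | 18% | 35% | 47% |
| Screen on level, baseline in the model | 7% | 13% | 20% |
| Screen on change | 72% | 84% | 90% |
| No screen, all candidates tested | 79% | 94% | 99% |

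The unscreened row is the highest. These percentages mainly reflect the number of tests; the screen does not create them.

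**Events for the logistic model.** If the outcome is inactive status at month 6 (an assumption):
- Exercise group: 447 × 0.185 = 83 events. At an assumed ten events per coefficient, that carries about 8 coefficients.
- Pooled: 447 × 0.185 + 447 × 0.276 = 83 + 123 = 206 events, or about 20 coefficients.
- Against 29 candidates: 83 / 29 = 2.9 and 206 / 29 = 7.1 events per candidate.

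The planned net fall is 447 × 0.091 = 41 men. It is not an event count, because men can move in both directions and the number who change status can be larger.

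**The case against.** The strongest reply is that the screen does less harm than it seems. With the level screen as worded, a noise candidate ends up as a determinant about 0.6–0.8% of the time overall, well below 5%, because few noise variables enter at all. Testing every candidate without a screen produces more false determinants. This stands. A reader might infer from the any-false-determinant percentages that removing the univariate gate would by itself lower them; the calculation shows the opposite. What remains is that the p-value and interval printed beside a selected variable do not have their stated properties, most clearly when screening is on change.

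A reader might also conclude that the logistic model is overfitted. The protocol does not support that as a fact: outcome, cut-off and candidate count are missing, and if few variables pass, 83 events may be enough. The pooled model is less exposed.

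A third tempting inference is that the determinants will be built into the service, because the Discussion says "This information can be utilized in future development of tailored gamified services". In context that refers to health status, fitness, motivational factors and profiles of active and inactive men. It does not name these models.

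Finally, cut-offs, candidate lists and validation are commonly left to an analysis plan. That is fair, and their absence is not the complaint. The complaint is about the selection rule that the protocol does state.

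**Conclusion.** The point holds as a minor one. The stated rule makes the nominal inference on selected variables invalid: about 12–14% instead of 5% for an entered noise variable when the screen is on level and baseline is left out, and about 49–68% when the screen is on change. The exact sizes depend on the assumed candidate count, cut-off and correlations. The direction does not: screening on the modelled response with correlation 0.3 between candidates still gave at least one false determinant in 41–46% of models. Overfitting of the exercise-group logistic model is possible and not established.

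Determinants of change appear in neither the objectives nor the hypotheses. The randomised comparison rests on t tests, repeated-measures analysis of variance and GEE, so it and its type I error are not affected.

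**What to change.** Replace the univariate gate in the Statistical analysis section with the following:

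- A short list of baseline variables per response, fixed before unblinding and kept in the model whatever their univariate result.
- The baseline value of the response always included. This removes the excess seen with the level screen; it was not checked as a remedy for a screen on change.
- For any logistic model, a named binary outcome and a list sized to its events (about 8 coefficients in the exercise group and 20 pooled, under the assumptions above).
- If the whole questionnaire is to be explored, penalised regression on all candidates with bootstrap validation, without nominal p-values.
- Results labelled exploratory.

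The cost is a change of wording and a little programming. Data collection, sample size and the primary analysis stay as they are. The price is fewer predictors and, on the penalised route, shrunken estimates without simple p-values.
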